##### Secondary outcomes

The first secondary outcome is the daily supine morning BP. This is measured and reported by the participants themselves before taking a seated position in bed.

During the four video sessions data is gathered on orthostatic BP through supervised home-based standing tests and daytime BP measured by the 24-h ABPM, which records daytime BP three times per hour. Other ABPM parameters will be considered as well (e.g., BP variability and nocturnal dipping).

Besides BP, the symptoms of orthostatic intolerance are determined with the Orthostatic Hypotension Questionnaire (OHQ) [30] and the cardiovascular questions of the Scales for Outcomes in Parkinson’s disease – Autonomic symptoms (SCOPA-AUT) [31]. Nocturia will be quantified during the ABPM measurement by collecting and reporting the total volume of urine produced during the night. On all other days, the overnight weight loss will be used to estimate the total volume lost. The International Consultation on Incontinence Questionnaire Nocturia Module (ICIQ-N) is used to determine the amount of bother experienced as a result of nocturia [32].

At both in-clinic sessions participants will be subjected to a phased tilt table test protocol including heart rate and beat-to-beat BP recordings (Finapres Medical Systems, Enschede, The Netherlands). We will tilt from a horizontal position to 15°, 30°, 45° and finally 60°. This will provide us with systematic measures of BP responses to different degrees of orthostatic positions. This, together with the standing test, will be used to investigate whether clinically relevant predictive values for the effectiveness of HUTS can be identified. Adverse events will be registered and grouped per treatment phase and group.

We selected several questionnaires which will be used to monitor the wellbeing of the participants in multiple areas:

The Pittsburgh Sleep Quality Index (PSQI) [33] to investigate sleep quality, duration and parasomnias, the number of falls during participation, and the fear of falling as determined by the Falls Efficacy Scale (FES) [34].The Parkinson’s Disease Questionnaire (PDQ-39) to evaluate mobility, activities, emotional wellbeing, stigma, social implications, cognitive impairment and bodily discomfort [35].The Hospital Anxiety and Depression Scale (HADS) [36] and the Mental Health Continuum-Short Form (MHC-SF) [37] to monitor the emotional wellbeing of the participants.

### Analysis

#### Interim analysis

The interim analysis will be used to provide information for a sample size calculation for a (phase III) follow-up study. No preliminary results with relation to the outcome of the study will be calculated. The average overnight BP from the first twelve participants will be used in this analysis. For these participants the change score comparing baseline (0°, week 1) and the 12° angle (week 5 or 7) will be determined, and only the average, standard deviation and confidence interval will be calculated. The researchers that are in contact with the participants will remain blinded to treatment groups, therefore this analysis will be performed by a non-blinded member of the research team. We will not use this analysis to terminate the study.

#### Final analysis

After completion of the study the data will be analyzed according to the intention-to-treat principles. For the main analysis of the overnight BP measured with the 24-hour ABPM in each phase we will use the overnight BP measured in week 1 as baseline to determine the change score. The 1° angle will serve as placebo, and the rest of the HUTS angles are grouped together for overall effectiveness and the increasing angles separately for determining which angle is the most effective for reducing the overnight BP. To estimate the effect of the HUTS angle we will use a linear mixed model with as a dependent variable the change in overnight BP as measured during the 24-hour ABPM, with fixed effects for angle, group and visit and with a random effect for subject. As covariables the baseline BP value, age and disease duration will be used. The within group differences will also be analyzed for all angles with a linear mixed effects model per group. Dependent variables in this calculation are the angle (fixed effect) and subject (random effect). The daytime variation will be calculated in the same way as described for the overnight BP.

The secondary outcome morning supine BP will be analyzed by averaging the three consecutive morning measurements and comparing the 13 timepoints from each phase with the baseline for overall effect, and by comparing each of the three phases to investigate the difference in effect for angles taking into account the time-effect.

Additional explorative analyses based on the per-protocol principles will be performed, this includes the analysis on tolerability of HUTS, baseline characteristics collected at the in-clinic sessions, the results from the PSQI, falls, FES, PDQ-30, HADS and MHC-SF which all will be exploratively analyzed. The tilt table test will be analyzed to investigate the differences between responders and non-responders by looking at the severity of supine hypertension and orthostatic hypotension.

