First, we will plan an in-clinic visit (either at the Radboudumc or LUMC). For consistency, this visit will always be scheduled in the early afternoon. Here, participants can ask additional questions and sign informed consent. The researchers will then gather baseline characteristics, perform their initial assessments with continuous BP measurements and several questionnaires. The assessments and questionnaires can be found in Table 1. Finally, the participant will be asked to install an app through which they can report their at-home measurements.After this session, the participants are randomized to one of the two groups. We will apply the randomization feature of the data management system Castor EDC with block sizes of two and four to allow the interim analysis. We will stratify based on gender. The researchers who perform the assessments and/or are involved in the analyses will remain blinded to the participant allocation during the study. Only the researchers who perform the randomization and deliver the materials at home will know which group the participants are allocated to. We will not inform the participants that we expect that the first angle in the delayed treatment group has no effect on BP regulation, making this a double-blind study.We will schedule an appointment to deliver all study materials within one week after the first session.Participants will perform daily at home measurements of supine BP and their weight. They will be asked to record their measurements in the app.We will schedule four video calls with the participants to discuss potential caveats and supervise the BP standing tests. Participants will also be asked to fill out several questionnaires in the app on this day and to disclose whether they slept in the prescribed angle. During this video check-in we will also guide the initiation of the 24-hour ABPM (Table 1).Participation ends with a follow-up in clinic session, also scheduled in the early afternoon for consistency, where the BP measurements and questionnaires from the first in clinic session are repeated and participants are asked about their experiences. When they want to proceed HUTS, they are offered to keep the materials and to do so under supervision of their primary care physician.

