#### Intervention

All participants in this study are subject to a six-week intervention. They will be sleeping in a whole-body HUTS position at three different angles, for two weeks each. The treatment group will sleep at HUTS angles of 6°, 12° and 18°. The delayed treatment group will first sleep at the placebo angle of 1° which is considered the control, after which they also sleep at 6° and 12° HUTS (Fig. 1). In both groups the intervention is preceded by a week of horizontal sleeping for baseline measurements.

The necessary materials will be delivered to the participants’ homes. To facilitate implementation in the home situation we have developed a frame that can be used to tilt the mattress into all different angles (Fig. 2A). For those who do not wish to use this frame, we offer wedge shaped mattresses with similar HUTS angles (Fig. 2B). The effect of HUTS on sleep quality is not yet known, but higher angles of HUTS may cause discomfort. Slipping can be reduced by increasing the friction of bedcover fabric, placing a rolled-up towel under the hips or in several other ways. We will expand this list as participants figure out what works for them during the study. We offer to provide each participant with a sleeping partner the frame for both so that they can sleep next to each other in the same angle during the trial. For good application of the HUTS method in the participant’s home, we will pay a home visit not only to deliver the materials, but also to offer support. For those who require or request extra help during the study we will provide this by offering a telephone or video call and, if necessary, by additional home visits.

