An additional methodological challenge due to the design of the study is the complexity of the statistical analyses. The order of the angles of the intervention are not randomized, which was chosen due to the impact that the order may have on the perception of the different angles. By increasing the tilt angles step by step, the participants can slowly get used to tilted sleeping. We hope this improves the tolerability of the higher inclinations and reduces dropouts due to uncomfortable sleeping. If they still do not tolerate a new, higher angle, we will ask participants to return to the previous angle. From a physiological perspective one would expect that the impact HUTS will increase proportionally to the size of the angle. Randomizing the order of the angles would require wash-out periods to evaluate the independent effect of each angle but also longer intervention periods for steeper angles to reach a steady state of the effect. We therefore preferred the fixed and incremental order of HUTS inclination as a more practical design. The intention-to-treat analysis is likely to influence our results for the efficacy of the higher angles; we will therefore perform an additional per-protocol analysis.

Orthostatic hypotension often results from multiple contributing factors that can be neurogenic and non-neurogenic. Autonomic dysfunction, nocturnal hypertension, nocturia, hypovolemia, BP medication or dopaminergic medication may all contribute to orthostatic hypotension, but we cannot study each factor separately or their interaction with each other. We will try, however, to identify hemodynamic markers to predict HUTS efficacy. We will also monitor the impact of HUTS on nocturia, an often neglected and incapacitating symptom in PD or parkinsonism. Interestingly, nocturia seems more prominent in persons with supine hypertension and may contribute to orthostatic intolerance, but no concise evidence exists [17]. By monitoring nocturia and including those with supine hypertension and orthostatic hypotension, we hope to uncover the complex interplay between these factors.

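### In the stated model, pooling 6°, 12° and 18° against 1° gives a near-zero or attenuated overall effect unless all active angles work equally well

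*Protocol article*

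**What the plan says.** Under Intervention, the treatment group sleeps at 6°, 12° and 18° in successive two-week phases. The delayed group has the "placebo angle of 1° which is considered the control, after which they also sleep at 6° and 12° HUTS". The 1° condition therefore fills one of the six group-by-phase cells.

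Under Final analysis, the outcome is "the change in overnight BP as measured during the 24-hour ABPM", taken from the week-1 baseline. On the comparison, the section says: "The 1° angle will serve as placebo, and the rest of the HUTS angles are grouped together for overall effectiveness". It adds that the increasing angles will also be examined separately. The model for the angle effect comes "with fixed effects for angle, group and visit and with a random effect for subject", with baseline BP, age and disease duration as covariates. A mixed model within each group is also planned. No other between-group model is given.

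Two statements bear on the expected dose-response. The Discussion says that "one would expect that the impact HUTS will increase proportionally to the size of the angle". Under Procedure, the article says that "we expect that the first angle in the delayed treatment group has no effect on BP regulation".

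**The concern.** A pooled active-versus-placebo term describes overall effectiveness only if the model compares active cells with placebo cells on an equal footing. Here every treatment-group cell is active, and the delayed group is on placebo only in its first phase. Once group and visit are in the model, the pooled term can be estimated only by comparing the delayed group's change after its first phase with the treatment group's change over the same interval. The treatment group is moving to steeper angles in that interval, so its further gain is subtracted as if it were a time trend.

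This is the main analysis of the primary outcome. The trial is meant to inform a phase III trial and the choice of its angles. An overall-effect estimate close to zero for a working intervention would misinform that step.

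**Working it through.** **Inputs.** The angle sequences come from Intervention and the model terms and grouping from Final analysis. The response shapes come from the Discussion (proportional) and Procedure (no effect at 1°), and the other shapes are assumed for illustration. Everyone is taken to sleep at the scheduled angle with complete data. The plan states no figure for the pooled effect, so there is none to reproduce.

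**Cells.** T is the treatment group, D the delayed group, and the number is the phase:

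- T1 = f(6), T2 = f(12), T3 = f(18)
- D1 = f(1), D2 = f(6), D3 = f(12)

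The pooled indicator is 0 in D1 and 1 in the other five cells.

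**Coefficient.** With group and three-level visit in the model, the indicator's coefficient is

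[(D2 + D3)/2 − D1] − [(T2 + T3)/2 − T1]
= ½f(6) + ½f(12) − f(1) − ½f(12) − ½f(18) + f(6)
= 1.5·f(6) − 0.5·f(18) − f(1).

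The weights sum to zero within each group, so subject-level covariates drop out. Generalised least squares on the six cells gave the same weights at every within-subject correlation tried.

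**Target.** The quantity the term should describe is the mean of the five active cells (6, 12, 18, 6, 12) minus the 1° cell. For a proportional effect that is 54b/5 − b = 10.8b − b = 9.8b, or 10.8b if f(1) = 0.

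| Response (mmHg) | Pooled coefficient | True average difference |
|---|---|---|
| Proportional, b per degree, including 1° | 9b − 9b − b = −b | 9.8b |
| Proportional, but f(1) = 0 | 9b − 9b = 0 | 10.8b |
| Saturating: 0, −4, −6, −7 | −6 + 3.5 = −2.5 | −27/5 = −5.4 |
| Convex: 0, −1, −5, −10 | −1.5 + 5 = +3.5 | −22/5 = −4.4 |
| Flat: 0, −6, −6, −6 | −9 + 3 = −6 | −6 |

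With visit as a linear term, the two proportional rows are unchanged.

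**Simulation.** This used 200 trials of 25 per group, with b = −1 mmHg per degree and between- and within-subject SDs of 8 mmHg, all assumed.

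- Proportional down to 1°: mean estimate +1.02 mmHg against a truth of −9.8. A significant benefit was found in 0.5% of trials.
- f(1) = 0: mean estimate +0.10 mmHg against −10.8. A significant benefit was found in 3.5% of trials.

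**Separate angles in the same model.** An intercept, three angle terms, one group term and two visit terms make seven columns. Their rank is six. If the angles are numbered 1 to 4, the step equals the phase in the delayed group and the phase plus one in the treatment group. A linear trend over angle steps therefore cannot be told apart from a visit trend plus a group difference.

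**The case against.** **The link is inferred.** The article states the grouping in one sentence and the model in the next, and does not say that the grouped contrast is an indicator in that model. This stands as a caveat. It remains the only between-group model given, so the inference is reasonable. Pooling alone is not the fault: without visit, the pooled term is 8b to 9.8b under proportionality, but it is then confounded with time because 1° always comes first.

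**Wrong sign.** A reader might infer that the plan would make an effective treatment look harmful. The documents do not support that in general. A reversed sign needs proportionality down to 1°, or a convex response, whereas Procedure expects no effect at 1°, which gives zero. The proportionality statement is a physiological argument for the ascending order and not a modelling assumption. Under Discussion, participants who do not tolerate an angle return to the previous one. If a share p of the treatment group returns from 18° to 12°, with no returns in the delayed group and proportionality down to 1°, the coefficient is (−1 + 3p)b. It has the right sign once p exceeds one third, but remains far below the true difference.

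**Other outputs.** A reader might also infer that the trial would conclude there is no effect. The plan also includes separate angles and within-group models, ties no decision rule to the pooled term, and acknowledges the fixed order and analytic complexity. These outputs do not repair the pooled estimate. The separate angles are not estimable in the stated model, and a within-group comparison of angles is confounded with time.

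**Conclusion.** The point holds in this form: read with the only between-group model given, the pooled contrast does not measure overall effectiveness unless all active angles act equally. Under the article's own expectation of a proportional effect it is near zero (0 or −b) where the true average difference is 10.8b or 9.8b. Under the saturating example it returns −2.5 mmHg against a true −5.4.

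The algebra needs no assumption about SD or correlation. It rests on scheduled angles being kept, complete data, and the grouped contrast being fitted with group and visit. The simulated figures depend on assumed effects and SDs, since the article gives neither.

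**What to change.** 1. Drop the pooled HUTS-versus-1° contrast as the measure of overall effectiveness.
2. Define the placebo-controlled effect as the randomised first-phase (weeks 2–3) difference between 6° and 1°, adjusted for baseline BP.
3. Estimate the separate angles with categorical angle, visit, baseline BP and a random subject effect, without the group term. This has six columns and rank six. It recovers each angle's effect relative to 1° whatever the dose-response shape, provided there is no carry-over and angle effects do not depend on visit. Randomisation supports leaving group out.
4. Give a per-degree slope, if at all, only as a secondary summary that assumes linearity. For a flat −6 mmHg effect, a slope model with visit and without group gives −0.18, −0.02 and +0.68 mmHg per degree at within-subject correlations of 0.5, 0.7 and 0.9.
5. State that only 6° has a concurrent placebo.

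The cost is a change of analysis wording plus some precision. The 12° and 18° effects become sums of two and three concurrent group differences. Assuming SD 12 mmHg, correlation 0.5 and 25 per group, the standard errors are:

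- 6°: √(2 × 144/25) = 3.4 mmHg
- 12°: √(2 × 144/25 × 3) = 5.9 mmHg
- 18°: √(2 × 144/25 × 6) = 8.3 mmHg

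The factors 3 and 6 are the variances of a sum of two or three values with correlation 0.5, in units of one value's variance. The 12° and 18° effects can then no longer be described as directly placebo-controlled.

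### With angle as a factor, the main mixed model's angle, group and visit terms are exactly collinear under the fixed schedule, so no pairwise angle comparison can be estimated

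*Protocol article*

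**What the plan says.** All places are in the protocol article.

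- **Outcome.** Under Final analysis, "we will use the overnight BP measured in week 1 as baseline to determine the change score". Week 1 is therefore used up as baseline, and each participant contributes three post-baseline phases.
- **Model.** The same section specifies a linear mixed model "with fixed effects for angle, group and visit and with a random effect for subject". It adds: "As covariables the baseline BP value, age and disease duration will be used".
- **Purpose.** The 1° angle is the placebo. The other angles are first pooled for overall effectiveness. The model is then to take "the increasing angles separately for determining which angle is the most effective for reducing the overnight BP". Separate models per group are also planned.
- **Analysis set.** After completion, "the data will be analyzed according to the intention-to-treat principles".
- **Schedule.** Under Intervention, "The treatment group will sleep at HUTS angles of 6°, 12° and 18" degrees, while participants in the delayed arm "first sleep at the placebo angle of 1° which is considered the control, after which they also sleep at 6° and 12° HUTS". The Discussion confirms: "The order of the angles of the intervention are not randomized".

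The Discussion acknowledges that the analysis is complex and the order fixed. It does not mention that the three fixed effects are linearly dependent.

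**The concern.** Both groups climb the same ladder of angles, and the delayed group is always exactly one rung behind. Once you know a participant's group and visit, you know the assigned angle, and the relation is additive: one rung per visit plus one rung for being in the treatment group. A model with additive terms for angle, group and visit therefore contains the same linear trend twice. It cannot say how much of that trend belongs to angle.

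The linear trend in angle is what the trial is after. The Discussion says the study will help determine which angles a phase III trial should focus on. If the main model cannot separate that trend from group and visit, the reported angle effects come from a constraint that nobody chose.

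**Working it through.** The article gives no figure on this point to reproduce. The check is of the design matrix implied by its stated terms and schedule.

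**Inputs from the article.** The angle schedule (Intervention); the fixed effects, covariates and intention-to-treat principle (Final analysis); 50 participants (Sample size calculation). **Assumptions, used for standard errors only:** 25 per group, SD of the change score 12 mmHg, within-person correlation 0.3, 0.5 or 0.7. The rank result needs none of these.

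**1. The identity.** Number the angles 1°, 6°, 12°, 18° as steps 0, 1, 2, 3, and code group 1 for treatment and 0 for delayed.

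| Group | Visit 1 | Visit 2 | Visit 3 |
|---|---|---|---|
| Treatment (1) | 6°, step 1 | 12°, step 2 | 18°, step 3 |
| Delayed (0) | 1°, step 0 | 6°, step 1 | 12°, step 2 |

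In every cell, step = (visit − 1) + group.

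**2. Angle as a factor.** Intercept 1 + angle 3 + group 1 + visit 2 = 7 columns for 6 cells; the rank is 6. The null vector is angle (+1, +2, +3), group −1, visit (−1, −2). Adding any multiple k of it leaves all six fitted means unchanged. Every pairwise angle contrast changes with k, so none is estimable. Only the two curvature contrasts survive: (12°) − 2(6°) + (1°) and (18°) − 2(12°) + (6°). Treating visit as linear does not help (6 columns, rank 5). Adding the three covariates gives 10 columns and rank 9; they are constant within a person and cannot break the identity, nor can the random subject effect.

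**3. What gets reported.** Illustrative truth: −3 mmHg per angle step and a drift d per visit. Each full-rank version fits all six cell means exactly. The table gives the estimate of 18° versus 1°.

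| Column dropped | d = 0 | d = −1 | d = −2 |
|---|---|---|---|
| Group | −9 | −9 | −9 |
| Either visit column | −9 | −12 | −15 |
| Any angle column | 0 | 0 | 0 |

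Dropping a visit column gives −9 + 3d. Dropping an angle column moves the whole linear trend into group and visit.

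**4. Angle in degrees.** Let T and D be the treatment and delayed cell means, numbered by visit. The between-group gaps are 5°, 6° and 6°. With group and visit in the model, the slope is

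½[(T2 − D2) + (T3 − D3)] − (T1 − D1), divided by 6 − 5 = 1 degree.

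It is identified only because the first gap is 5° and not 6°. Its standard error is 12 × √[(2/25) × 1.5 × (1 − ρ)].

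| ρ | SE with group (mmHg/°) | SE without group | Ratio |
|---|---|---|---|
| 0.3 | 3.48 | 0.43 | 8.0 |
| 0.5 | 2.94 | 0.48 | 6.1 |
| 0.7 | 2.28 | 0.52 | 4.4 |

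**5. Pooled active versus placebo.** With group and visit in the model, the coefficient is (T1 − D1) − ½[(T2 − D2) + (T3 − D3)]. If the effect is −3 per step, this is −3 − ½(−3 − 3) = 0. Without group the bias remains: the estimate is −1.6, −1.0 and −0.5 at ρ = 0.3, 0.5 and 0.7, against a true 6° versus 1° effect of −3.

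**6. Angle (4 levels) + visit (3 levels), no group.** 6 columns, rank 6 (9 of 9 with covariates). Then 6° vs 1° = T1 − D1, 12° vs 6° = T2 − D2, and 18° vs 12° = T3 − D3. The standard errors against 1° are 12 × √(2/25) times 1, √(2 + 2ρ) and √(3 + 6ρ). At ρ = 0.5 these are 3.39, 5.88 and 8.31 mmHg. The ratio of 18° to 6° is √(3 + 6ρ) = 2.19, 2.45 and 2.68 at ρ = 0.3, 0.5 and 0.7.

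**The case against.** **The coding is not stated, and a condensed article may leave it to the full plan.** This stands as a limit. Singularity holds for angle as a factor or an equal-step score, not for degrees or for a pooled active term. The Discussion also expects an effect proportional to the angle, which is compatible with degrees. But a placebo angle and angles examined separately point to a factor. The full-rank codings give either a very imprecise slope or a pooled coefficient that misses a linear effect. The three terms are stated here, and they conflict with the stated schedule.

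**A reader might infer that the trial cannot estimate any angle effect.** The documents do not support that. The randomised 6° versus 1° comparison in the first tilt phase is available from the data whatever happens to this model, and the two curvature contrasts remain estimable. The per-group models contain only angle and subject, so their estimates are unique. They are confounded with time, not arbitrary.

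**A reader might also take the −15 as the expected size of error.** It rests on an assumed drift of −2 mmHg per visit; the article gives none. With no drift, dropping group or a visit column gives the same −9. The 0 needs no drift, but it does need an angle column to be the one dropped.

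**Participants who step back to a lower angle would break the identity.** They would if the actual angle were coded. The main analysis follows intention to treat, and identification would then rest on those who did not tolerate the angle.

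**Dropping group is not assumption-free.** This stands. After the first tilt phase the groups have different exposure histories, and the Discussion itself raises wash-out and time to steady state.

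**Conclusion.** The point holds in this form: the main model as written is not usable for comparing angles. With angle as a factor it has 7 columns of rank 6 and no estimable pairwise angle contrast. This is algebra and needs no assumption about variance, drift or sample size. With angle in degrees the slope is defined, but its standard error is about 4 to 8 times larger than without group, at assumed correlations of 0.7 to 0.3. Pooled active versus placebo is defined but returns 0 under an effect linear in step.

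This is a phase II trial with no formal sample size, so no power claim is at issue. The angle comparison is nevertheless a stated aim of the main analysis and is meant to inform phase III, so the model should be corrected before the data are analysed.

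**What to change.** Remove the group main effect from the main model and fit: change = angle (4 levels) + visit (3 levels) + baseline blood pressure + age + disease duration + random subject. Randomisation and the baseline covariate support leaving group out.

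Alongside it:

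- State the identifying assumption: no carry-over or exposure-duration effect beyond current angle and visit. Only 6° versus 1° in the first tilt phase is free of it.
- Base the overall-effectiveness claim on that randomised first-phase comparison, or on a stated average of the angle contrasts from this model. Do not use a pooled active/placebo term; deleting group does not repair it.
- Label the per-group models descriptive, because angle and time coincide in them.

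The change to the model statement is one term, plus the wording above. The cost is precision: the interval for 18° versus 1° is wide because it sums three between-group differences (standard error about 2.2 to 2.7 times that of 6° versus 1° at assumed correlations 0.3 to 0.7). In addition, six parameters for six cells saturate the mean model, so the data cannot test the carry-over assumption.

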A non-pharmacological and non-invasive intervention that can improve both orthostatic hypotension and possibly also supine hypertension is head up tilt sleeping (HUTS). The concept of HUTS is based on clinical observations made over 80 years ago [18–20]. These observations showed symptomatic and objective improvement of orthostatic hypotension during daytime. However, thus far HUTS has only been investigated in small and largely observational cohort studies, and never in a population with movement disorders [21–24]. The optimal tilt angle of HUTS is currently unknown but based on the presumed gravitational effect a steeper head-up tilt sleeping position is likely to be most effective, but is also less tolerable due to more discomfort in the sleeping position. The studied angles showing improved orthostatic tolerance varied from 12° to 40° [18, 19, 21–23], yet these studies did not evaluate the impact on nocturnal supine hypertension. This could be attractive, however, because from a physiological perspective, one would expect a more marked effect on supine hypertension rather than on orthostatic hypotension. HUTS will likely alleviate supine BP due to direct gravitational effects while orthostatic BP improvement is mediated by changes in extracellular fluid compartments. Accordingly, a placebo controlled RCT applying low HUTS angles (5°) found no effect on orthostatic hypotension, but more frequent occurrence of ankle oedema in the intervention group. This suggests that even a modest angle has potential to reduce supine hypertension [25, 26]. In clinical practice, HUTS is often not recommended, and when it is modest tilt angles are suggested with presumably at best also modest effects, as a guideline on practical implementation is still lacking [25, 26].

We here describe the design of the Heads-Up study, in which we investigate the potential efficacy and tolerability of different angles of HUTS as a treatment for both supine hypertension and orthostatic hypotension in people with PD. We will evaluate the effect of different angles of HUTS on several BP outcomes, orthostatic intolerance, compliance, tolerability, nocturia, as well as motor- and non-motor PD symptoms. Finally, we will explore whether certain participant characteristics may predict the effectiveness of HUTS.

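### The primary model assumes one variance at all three visits; if individual response varies in proportion to tilt angle, reported standard errors would be too large for 6° v 1° and too small for 18° v 12°

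*Protocol article*

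**What the plan says.** The Final analysis section fixes the outcome of the main model: "we will use the overnight BP measured in week 1 as baseline to determine the change score". Each participant therefore contributes three change scores. The model has terms "with fixed effects for angle, group and visit and with a random effect for subject", and "As covariables the baseline BP value, age and disease duration will be used". The section names no random slope and no variance that differs by visit, and the separate within-group models again have subject as the only random effect.

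Under Intervention, the treatment group moves through 6°, 12° and 18° in that order. For the other arm: "The delayed treatment group will first sleep at the placebo angle of 1° which is considered the control", followed by 6° and 12°. Angle and visit therefore rise together in both groups.

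The Discussion says that "one would expect that the impact HUTS will increase proportionally to the size of the angle". The Background adds that "we will explore whether certain participant characteristics may predict the effectiveness of HUTS", and the Final analysis section plans an exploratory comparison of responders with non-responders. The model is to be used for all tilted angles together against 1°, and also for "the increasing angles separately for determining which angle is the most effective for reducing the overnight BP".

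**The concern.** A single random subject effect is ordinarily a random intercept. It gives every change score the same variance and every pair of visits the same correlation. That fits poorly if people differ in how strongly they respond per degree, because the spread of responses then widens from 1° to 18°. Visit 1 (1° and 6°) would be the least variable and visit 3 (12° and 18°) the most.

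In an angle-plus-visit model each step between neighbouring angles is estimated by the difference between groups at one visit. A variance pooled over visits is then too large for the visit-1 step and too small for the visit-3 step. The visit-1 step, 6° v 1°, is the direct randomised comparison with the placebo angle. The visit-3 step bears on whether the steepest angle adds anything. The article uses the model to rank angles, and it intends the trial to guide the choice of angles for phase III.

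Returning participants to the previous angle when a higher one is not tolerated (Discussion) could be a further source of unequal spread in the later visits under intention-to-treat.

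**Working it through.** **Plan's own figure.** There is none to reproduce. The article gives 50 participants without a formal calculation, and no SD, correlation or standard error.

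**Inputs.** From the article: 50 participants, angles 1/6/12° and 6/12/18° at visits 1/2/3. Assumed: 25 per group, complete data, covariates already adjusted for, other between-person SD 8 mmHg, night SD s = 6 or 8 mmHg, individual slope SD b = 0.25, 0.5 or 0.75 mmHg per degree. At b = 0.5 the SD of individual response is 6 mmHg at 12° and 9 mmHg at 18°.

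**Mean model.** Angle (4 levels), group and visit as factors give 1 + 3 + 1 + 2 = 7 columns for 6 group-by-visit cells, with rank 6, because the angle step is visit plus group. No pairwise angle contrast is estimable from that set. I therefore used angle + visit (6 parameters, 6 cells).

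**Formulas.** True variance at angle a: 64 + s² + b²a². The random-intercept fit converges on the average of the six cell variances, V.
- Reported SE of a between-group contrast at one visit: √(2V/25).
- True SE: √((V_treatment + V_delayed)/25), using the variances of that visit.

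**Example, b = 0.5, s = 6.** Cell variances are:
- delayed group: 100.25, 109, 136
- treatment group: 109, 136, 181

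V = 771.25/6 = 128.54.
- Reported, either contrast: √(2 × 128.54/25) = 3.21.
- True, 6° v 1°: √(209.25/25) = 2.89; ratio 1.11.
- True, 18° v 12°: √(317/25) = 3.56; ratio 0.90.

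**Range.**

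| b | s | reported SE | true 6° v 1° (ratio) | true 18° v 12° (ratio) |
|---|---|---|---|---|
| 0 | 6 or 8 | – | (1.00) | (1.00) |
| 0.25 | 6 | 2.93 | 2.84 (1.03) | 3.03 (0.97) |
| 0.25 | 8 | 3.29 | 3.21 (1.02) | 3.38 (0.97) |
| 0.5 | 6 | 3.21 | 2.89 (1.11) | 3.56 (0.90) |
| 0.5 | 8 | 3.54 | 3.26 (1.09) | 3.86 (0.92) |
| 0.75 | 6 | 3.62 | 2.97 (1.22) | 4.30 (0.84) |
| 0.75 | 8 | 3.92 | 3.33 (1.18) | 4.56 (0.86) |

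Nominal 95% intervals then cover about 97% and 92–93% at b = 0.5, and about 98% and 90–91% at b = 0.75.

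**18° v 1°.** This contrast is the sum of the three visit differences, so its variance uses every variance and covariance. The random-intercept fit preserves their total, and the ratio is 1.00 at every b (8.44 v 8.44 in the example).

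**Does an unstructured covariance repair it?** With visit covariances pooled over equal groups, the two contrasts return to 2.89 and 3.56 exactly. The mean change at 18° in the treatment group does not. Pooled visit-3 variance is (181 + 136)/2 = 158.5, giving √(158.5/25) = 2.52 against a true √(181/25) = 2.69 (ratio 0.94). Over the range in the table that SE stays 2–9% too small.

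**The case against.** The strongest objection is that the premise is not in the article. The Discussion says that the effect grows with angle; it does not say that differences between people do. The responder comparison is exploratory and says nothing about variance by angle. That stands, and the point is therefore conditional: without slope variation every ratio is 1.00.

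Second, a condensed article may leave residual covariance, estimation method and degrees of freedom to an analysis plan, and this one does not exclude unequal variances or robust standard errors. This stands against any claim that the plan forces equal variance. It does not remove the point, because the article does state a random structure, and its ordinary reading has the consequence shown.

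Third, the effect is selective. Besides 18° v 1°, the comparison of all tilted angles with 1° is little affected: at b = 0.5 its reported SE is 2–3% too large with visit in the model, or about 2–4% too small with group and visit. This also stands.

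Fourth, a reader might infer that the placebo comparison loses precision, as if participants were thrown away. It does not. The angle-plus-visit model has as many parameters as cells, so with complete data the 6° v 1° estimate and its true SE are the same under either covariance. Only the reported interval is too wide.

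Finally, a reader might call rank deficiency the more basic defect. It is a separate matter, but repairing the mean model leaves the covariance question open.

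**Conclusion.** The point holds in conditional form. The stated random structure, on its ordinary reading, assumes equal variance across visits in a design where angle rises with visit. If response per degree varies between people, the reported SE is too large for 6° v 1° and too small for 18° v 12°. The errors run from 2–3% and about 3% to 18–22% and 14–16% over the assumed slope SDs. All SDs are assumptions, and the calculation takes equal groups and no dropout.

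Two stronger readings are not supported: that the plan itself expects individual differences to grow with angle, and that all intervals involving 18° are too narrow. Priority is optional to moderate for a phase II trial that is meant to inform phase III.

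**What to change.** State an estimable mean model, for example angle and visit as factors plus baseline blood pressure, age and disease duration. Fit it by REML with an unstructured covariance over the three post-baseline visits and Kenward-Roger degrees of freedom. Name heterogeneous compound symmetry as the fallback if the fit does not converge.

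For within-group estimates, such as the mean change at 18°, use a group-specific covariance or a random slope on angle. The groups sit at different angles at each visit, so the pooled visit covariance is not enough there.

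The cost is a change of model wording. The unstructured covariance has six parameters against two for the random intercept, so four more, with slightly fewer degrees of freedom. If variances prove equal, little is lost.
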